## Abstract

**Background:**

The co-occurrence of hypertension and abnormal glucose metabolism—a spectrum encompassing prediabetes and diabetes—substantially elevates the risk of cardiovascular disease (CVD). Effective management of this high-risk clinical overlap remains a therapeutic challenge. Yiqi-Shengjin granules (YQSJ), a traditional Chinese herbal formulation, have been employed as a hospital preparation at Beijing Hospital of Traditional Chinese Medicine for over three decades, primarily for the management of glucose metabolism disorders, with an annual treatment cohort exceeding 1,000 patients. Although preliminary clinical observations suggest potential benefits of YQSJ in patients with hypertension complicated by diabetes, robust evidence from standardized clinical trials is lacking. Therefore, a well-controlled clinical study is warranted to systematically evaluate the efficacy and safety of YQSJ in this specific population.

**Methods/design:**

This will be a randomized, double-blind, placebo-controlled study. After being screened and providing signed informed consent, participants will be evenly assigned to experimental or control groups in a 1:1 ratio. The experimental group will receive YQSJ 3 g twice daily and losartan 50 mg once daily, whereas the control group will receive YQSJ placebo 3 g twice daily and losartan 50 mg once daily. The treatment period will last for a total of 8 weeks (56 days), with follow-up visits scheduled every 2 weeks. The primary endpoint will be the difference in drug efficiency between the two groups. The secondary endpoints include 24 h blood pressure indicators, glucose metabolism indicators, lipid metabolism indicators, vascular damage indicators, insulin resistance indicators, oxidative stress indicators, and major adverse cardiovascular events (MACE). Safety and efficacy outcomes will be assessed both before and after the 8-week medication period.

**Discussion:**

This study aims to provide clinical evidence on the efficacy and safety of YQSJ in the treatment of hypertension in patients with abnormal glucose metabolism. Furthermore, we will explore the potential mechanism through which YQSJ might exert hypotensive effects and adjust glucose metabolism by examining pertinent indicators of vascular and oxidative stress, as well as its influence on clinical symptoms, risk factors associated with hypertension, and the target organs affected by this condition.

**Clinical Trial Registration:**

identifier ChiCTR2200062453.

## Backgrounds

The co-occurrence of hypertension and abnormal glucose metabolism—encompassing prediabetes and diabetes—poses a significant and escalating global cardiovascular challenge (1, 2). This combination synergistically amplifies the risk of major adverse cardiovascular events, creating a complex therapeutic landscape (3, 4). While conventional antihypertensive agents remain foundational, their limited impact on glycemia and associated side effects underscore the need for complementary strategies that address both conditions simultaneously (5–7).

Traditional Chinese Medicine (TCM), with its holistic approach and multi-target mechanisms, offers a unique paradigm for managing complex conditions like hypertension combined with glucose metabolism disorders. Historical records in ancient texts such as the Huangdi Neijing describe syndromes related to these conditions, and modern clinical practice continues to utilize TCM formulations for their management (8, 9). For instance, clinical studies have demonstrated the efficacy of specific TCM preparations, such as Songling Xuemaikang Capsule for blood pressure reduction in hypertensive patients (10) and Xiaoke Decoction for improving glycemic control (11), underscoring the potential of TCM in this field.

Yiqi-Shengjin Granules (YQSJ) is a hospital-prepared TCM formulation (Approval No. Z20053315). It has been clinically applied for over 30 years at Beijing Hospital of Traditional Chinese Medicine, a leading national TCM institution whose cardiovascular department is recognized as a Key National TCM Specialty. YQSJ is annually administered to over 1,000 patients for conditions related to hypertension and glucose metabolism disorders (12). The formula comprises ten medicinal herbs, including Panacis Quinquefolii Radix, Astragali Radix, Scrophulariae Radix, Citri Sarcodactylis Fructus, Lycii Fructus, Dendrobii Caulis, Amomi Fructus, Ophiopogonis Radix, Polygonati Odorati Rhizoma, Polygonati Rhizoma (13). All of them are listed as safe for use in health foods by the National Health Commission of the People's Republic of China (https://www.nmpa.gov.cn/).

Preclinical and pharmacological research provides a scientific basis for its application. YQSJ has been shown to significantly reduce random blood glucose and the insulin resistance index in spontaneous type 2 diabetic KKAy mice (14). Bioactive components of YQSJ, such as Ginsenoside Rg1, Harpagoside, and Calycosin-7-O-β-D-glucoside, have been identified in patient serum following administration (13). Network pharmacology and molecular docking analyses suggest that its core mechanism may involve modulation of the IRS-1/PI3K/AKT signaling pathway (13), a key pathway in both glucose metabolism and cardiovascular function. Several individual components of YQSJ have also been independently reported to possess antihypertensive properties (15–17). Pharmacological evidence indicates that these herbal components may improve endothelial function, reduce oxidative stress, and enhance insulin sensitivity. Furthermore, the formula has been included in a regional medical innovation promotion database, and previous clinical trials have explored its efficacy in prediabetes (18), diabetic cardiomyopathy (19), and stable angina (20).

Despite its long-term clinical use and promising preliminary data, robust evidence from randomized controlled trials regarding the efficacy and safety of YQSJ specifically for hypertension in patients with abnormal glucose metabolism is lacking. To address this gap, we designed this randomized, double-blind, placebo-controlled clinical trial. The present article details the study protocol.

## Methods

### Objectives

This study aims to assess the clinical effects of YQSJ on blood pressure in patients with abnormal glucose metabolism and to provide a reliable experimental basis for the treatment of hypertension and impaired glucose metabolism.

### Design

This is an exploratory study with a randomized, double-blind, placebo-controlled design. All protocol modifications were made before participant enrollment to improve feasibility, ensure operational consistency, and comply with ethics requirements. They were planned and implemented by the study team, reviewed and approved by the ethics committee, as detailed in Supplementary Material.

After screening and voluntarily signing the informed consent form, 72 participants recruited from the Beijing Hospital of Traditional Chinese Medicine will be randomly and evenly assigned into the experimental and control groups on the basis of the randomized numerical table generated by SAS software.

The experimental group will be treated with YQSJ 3 g twice a day and losartan 50 mg once a day, whereas the control group will be treated with YQSJ placebo 3 g twice a day and losartan 50 mg once a day. The patient's basic drug regimen remained unchanged. The treatment will last 8 weeks (56 days) in total, with follow-up visits every 2 weeks. Safety and efficacy indicators will be observed before and after 8 weeks of medication (Figure 1).

**Figure 1 F1:**
[figure not shown]
Flowchart of this study.

### Recruitment

Participants will recruit from Beijing Hospital of Traditional Chinese Medicine through notices in hospital and newspapers. Advertisement approved by the Research Ethics Committee will be used to promote enrollment. The principal investigator, together with a well-trained attending physician, will identify potential patients on the basis of the eligibility criteria. All the included participants were informed face to face of the entire study according to the Research Ethics Committee and voluntarily signed the informed consent form.

The eligibility criteria for the study participants were as follows:

Inclusion criteria: patients who met all of the following criteria.
Understand the process of this trial and provide informed consent.Patients were diagnosed with impaired fasting glucose, abnormal glucose tolerance or type 2 diabetes mellitus in accordance with the ADA standard (3), and HbA1c < 8% within the past 2 weeks.The patient was diagnosed with primary hypertension (grade 1–2) in accordance with the AHA standard (1). It is defined as systolic blood pressure (SBP) of 140–179 mmHg and/or diastolic blood pressure (DBP) of 90–109 mmHg.Male aged between 18 and 75 years.Exclusion criteria: Patients who met any of the following criteria.
Severe infection, trauma and/or recent or planned surgery.Severe conscious impairment, severe cognitive dysfunction, or severe psychiatric disorders;Those with other comorbidities, such as chronic kidney disease and liver disease (hepatic inadequacy: alanine amino transferase or alkaline phosphatase levels more than twice the upper normal limit). Renal inadequacy: serum creatinine level ≥133 mmol/L)Withdrawal criteria: Patients who met any of the following criteria.
Discrepant the eligibility criteria after inclusion.The participants were asked to withdraw.Allergic reactions, serious adverse reactions, adverse events, or intoleranceUnable to perform the test as needed (poor compliance).

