### Randomization and blinding

All the enrolled patients were included in the clinical trial according to the order of random table numbers from the numerical table generated by SAS software. The ratio of the experimental group to the control group is 1:1.

For blinding, the allocation code for each participant will be placed in opaque envelopes. The envelopes also contain details of the treatment options, possible adverse events, and emergency measures. The envelopes and treatment plans of each participant will not be accessible to all the researchers or participants. The drug and the placebo are similar, and the manufacturer will label the random codes on the package according to the principles of GCP.

Each coded experimental drug is accompanied by a corresponding emergency letter containing a slip of paper indicating the type of the coded drug to be used in the event of an emergency to break the blind. The emergency letters were sealed and sent to each clinical trial center with the corresponding numbered test drug, which is responsible for keeping it and should not be opened unless necessary. It should be opened by the investigator in the event of an emergency, or if the subject requires resuscitation, it is necessary to know what treatment the subject is receiving. Once opened, the numbered subject will be withdrawn from the trial and treated as a shedding case, and the investigator will record the reason for withdrawal on the case report form. All contingency letters will be retrieved with the case report form at the end of the trial for blinded review at the end of the trial.

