### Endpoint measurements

#### Primary endpoint

The primary endpoint is the difference in drug efficiency between the two groups. Efficiency is defined as follows: blood pressure is reduced to a threshold set out in the Guiding Principles for Clinical Research of New Chinese Medicines (21). The level of glycosylated hemoglobin is decreased by at least 2% (22).

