#### Data analysis

SPSS 15.0 (PN: 32119001, SN: 5045602) will be used for statistical analysis. The measurement data are expressed as the means ± standard deviations. Between-group comparisons of two groups of normally distributed and variance-aligned continuous variables were performed via t tests. Comparisons between groups of two normally distributed continuous variables with chi-square variance between each stratum will be performed via analysis of variance (ANOVA) with randomized area group design data, and two-by-two comparisons between multiple groups will be performed via the SNK-q test. Comparisons between groups of nonnormally distributed continuous variables will be performed via the rank sum test. Comparisons between groups of count data were performed via the chi-square test, and Fisher's exact probability test will be used when the expected frequency is <5. Major adverse cardiac events will be evaluated via Cox regression analysis. *P* < 0.05 is considered a statistically significant difference. Baseline blood pressure levels will be included as covariates in the statistical analysis to minimize potential confounding effects.

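### The primary responder comparison, which depends partly on HbA1c, is not adjusted for glycaemic category at entry, although prediabetes and type 2 diabetes are pooled and the category is likely to be prognostic

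*Protocol article*

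**What the plan says.** All references are to the protocol article.

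- **Recruitment.** The entry criterion reads "Patients were diagnosed with impaired fasting glucose, abnormal glucose tolerance or type 2 diabetes mellitus", with HbA1c below 8%. No quota or expected split between prediabetes and diabetes is given. Only men are eligible.
- **Primary endpoint.** A responder is defined by a blood pressure threshold taken from a guideline and by an HbA1c criterion: "The level of glycosylated hemoglobin is decreased by at least 2" percent. The text does not say whether the percentage is relative or absolute, or whether a patient must meet both parts or either.
- **Design; Randomization and blinding.** Patients enter "according to the order of random table numbers from the numerical table generated by SAS software", and "The ratio of the experimental group to the control group is 1:1". No stratification factor is named.
- **Sample size calculation.** One overall responder rate per arm is assumed, 30% and 65%. There are 27 evaluable and 36 enrolled patients per arm.
- **Data analysis.** "Comparisons between groups of count data were performed via the chi-square test", with Fisher's test for small expected counts. The last sentence of the section adds baseline blood pressure as a covariate. Glycaemic category and baseline HbA1c are not mentioned as covariates.

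**The concern.** The responder rule has a blood pressure part and a glycaemic part. The plan names a baseline covariate for the first and none for the second, although the entry criterion itself sorts patients by glycaemic status. A patient with prediabetes starts from a lower HbA1c than most patients with diabetes, so the chance of meeting the HbA1c part may well differ between the categories.

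If it does, two things follow in a trial of 72. First, an unadjusted comparison leaves explainable variation in the outcome and gives up some power. Second, the diabetic share can differ between arms by chance, and an unadjusted estimate then mixes that difference with the effect of YQSJ. The diagnosis is needed to establish eligibility, so the information is there without any new data collection.

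**Working it through.** **1. The plan's own figure.** Inputs from the sample size section: 30% v 65%, one-sided α 0.025, 80% power, 1:1, margin 0. Exact enumeration of the unpooled Z test gives 78.2% power at 26 per arm and 80.6% at 27, so 27 is reproduced. For the pooled chi-square test, exact power is 72.4% at 27 per arm and 85.2% at 36. If 20% of 36 drop out, 36 × 0.8 = 28.8, about 29 per arm, remain.

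**2. Assumptions.** The article gives neither the diabetic share nor responder rates by category. I assume a 50% diabetic share and a gap g between categories, the same in both arms, with overall rates held at 30% and 65%. Category rates are then p ± g/2. For g = 30 points this gives 15% and 45% in the control arm, 50% and 80% in the experimental arm.

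**3. Power.** Simulation with 200,000 trials per setting and allocation without stratification; pooled chi-square v CMH stratified by category, one-sided 0.025:

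| Per arm | gap 0 | gap 20 | gap 30 | gap 40 |
|---|---|---|---|---|
| 27 | 72.4% v 73.2% | 72.3% v 75.5% | 72.4% v 78.6% | 72.4% v 82.5% |
| 29 | 77.3% v 77.0% | 77.4% v 78.9% | 77.5% v 81.5% | 77.1% v 85.1% |
| 36 | 85.0% v 85.1% | 85.1% v 87.1% | 85.2% v 89.2% | 85.0% v 91.9% |

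The change at 29 per arm is −0.3, +1.5, +4.0 and +8.0 points. At 36 per arm it is +0.1, +2.0, +4.0 and +6.9.

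**4. How often the arms differ.** The standard deviation of the difference in diabetic share is √(2 × 0.5 × 0.5 / n): 0.118 at n = 36 and 0.131 at n = 29. A difference of at least 10 points occurs in about 41% of trials at 36 per arm and 51% at 29. A difference of at least 20 points occurs in about 8% and 15%.

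**5. Type I error.** Averaged over randomisations, both tests stay near the one-sided 0.025. Given a particular imbalance, they differ. Take 22 v 14 diabetics of 36, a 30-point gap and no treatment effect. Expected response is (22 × 0.45 + 14 × 0.15)/36 = 33.3% in the experimental arm and (14 × 0.45 + 22 × 0.15)/36 = 26.7% in the control arm, a spurious difference of 6.7 points. The one-sided false-positive rate is about 8.0% for chi-square and 2.6% for CMH. With the imbalance reversed and the assumed treatment effect present, power is 68% v 87%.

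**The case against.** Several counter-arguments carry weight.

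- **Silence in a condensed article.** A reader might infer that randomisation is known to be unstratified. The article does not say so. It names no factor, and the sample size section hints at blocks. The full protocol or the analysis plan may name factors or further covariates. This stands, so the point rests on the analysis as stated, not on the randomisation.
- **The plan does adjust.** Calling the primary analysis a plain chi-square ignores the sentence on baseline blood pressure. That stands too. A chi-square test cannot carry a covariate, so the section does not settle how the primary comparison is made. A test stratified by glycaemic category alone would also drop a covariate to which the plan commits. The blood pressure covariate does not, however, address glycaemic status.
- **Prognostic strength is assumed.** A reader might infer that category is a known prognostic factor and that power is certainly lost. No responder rates by category are given, and at a gap of 0 nothing is gained. The strength also depends on the unresolved HbA1c rule. If the fall is absolute and both parts are required, few patients with prediabetes could respond. With half the patients diabetic, overall response could then hardly exceed 50%, which is incompatible with the assumed 65%. The power table does not apply under that reading.
- **No bias on average.** A reader might infer that chance imbalance invalidates the test. It does not: overall type I error is kept. Typical shifts are also modest. A 13-point imbalance with a 20-point gap moves the estimate by 0.13 × 20 = 2.6 points, against a standard error of √[(0.30 × 0.70 + 0.65 × 0.35)/29] = 12.3 points.
- **Context.** The trial is called exploratory, and the Limitations section concedes that power may be limited and heterogeneity not fully captured. That lowers the stakes but is no reason to leave out an adjustment that costs almost nothing.

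**Conclusion.** The point holds as a recommendation to improve the primary analysis. The article pools prediabetes and type 2 diabetes, uses HbA1c in the responder rule, and describes no adjustment for glycaemic status. Under gaps of 0 to 40 points, a 50% diabetic share and overall rates of 30% and 65%, adjustment changes power by about 0 to +8 points at 29 per arm and 0 to +7 at 36. Larger gains require gaps of 30 points or more, which nothing in the article confirms.

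The firmer argument is protection of the one trial actually run. If the arms turn out uneven and the category matters, the unadjusted test can be well off its nominal level in either direction. The document does not support the stronger claims that randomisation was unstratified, that category is an established prognostic factor, or that the unadjusted test has an inflated error rate overall.

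**What to change.** Before unblinding, state that the primary responder comparison is adjusted for glycaemic category at entry (prediabetes v type 2 diabetes) or for baseline HbA1c, together with the baseline blood pressure covariate already planned. Logistic regression with a standardised risk difference and 95% confidence interval would do this. A CMH test stratified by glycaemic category, with its weighted risk difference, is an alternative if baseline blood pressure is handled separately. Choose one in advance. Keep the unadjusted chi-square as a sensitivity analysis and report responder rates by category and arm.

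The HbA1c criterion (relative or absolute, joined by and or by or) also has to be settled, because the value of the adjustment depends on it.

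The cost is a sentence or two in the Data analysis section. No new data or patients are needed. Randomisation stays as it is, which matters because the Trial status section reports 40 patients already recruited. If category is unrelated to response, the loss with CMH is at most about 0.3 points of power at 29 per arm (77.3% v 77.0%).

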### Intervention

YQSJ (production batch number 181201) and YQSJ placebo (production batch number 181202) were produced and packed in a single batch by the Beijing Institute of Traditional Chinese Medicine. According to the preparation process, 1 g of the finished granules corresponds to approximately 1.67 g of crude herbal materials. Each bag of YQSJ contained 5 g of crude drug. The dosage is consistent with the recommended dosage in previous pharmacology studies and clinical practice (13). As tested, the drug conformed with the quality specified in the Chinese medicine standards published by the State Food and Drug Administration. Phytochemical analysis via LC-MS performed by Beijing Hexin Technology Co., Ltd. was used to identify the constituent compounds. The total ion chromatogram of Liquid chromatography-mass spectrometry, plant sources and compounds were presented in Supplementary Figures S1–S2 and Table S1–S2). Losartan will be purchased from the Pharmaceutical Branch of China Pharmaceutical Holdings Beijing Co., Ltd. (Unified Social Credit Identifier 91110101101297579G).

The experimental group will be treated with YQSJ 3 g twice a day and losartan 50 mg once a day, whereas the control group will be treated with YQSJ placebo 3 g twice a day and losartan 50 mg once a day. The patient's basic drug regimen remained unchanged. The treatment will last 8 weeks (56 days) in total, with follow-up visits every 2 weeks. Safety and efficacy indicators will be observed before and after 8 weeks of medication.

All participants will receive losartan as the background antihypertensive therapy throughout the study period. The use of other antihypertensive medications will be prohibited unless clinically necessary. If additional antihypertensive treatment is required due to uncontrolled blood pressure or safety concerns, the participant will be managed according to clinical judgment and may be withdrawn from the study if necessary. Medication adherence will be monitored through regular follow-up visits, drug accountability records, and patient self-reports to ensure compliance with the study protocol.

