#### Secondary endpoints

24-h blood pressure indicators: average SBP, DBP, mean arterial pressure (MAP), blood pressure variability and circadian blood pressure amplitudeGlucose metabolism indicators: fasting blood glucose, 2 h postprandial blood glucose, glycosylated hemoglobin, CMI = WHtR × [TG (mmol/L)/HDL-C (mmol/L), WHtR = waist circumference (cm)/height (cm) (23), HOMA-IR = FBG (mmol/L) × FINS (μU/mL)/22.5 (24)Lipid metabolism indicators: triglycerides, cholesterol, LDL, HDLVascular damage indicators: vascular endothelial function markers, brachial and ankle artery pulse wave velocity, ankle-brachial indexThe oxidative stress indicators: superoxide dismutase (SOD) and malondialdehyde (MDA).Major adverse cardiovascular events (MACEs) and disease regression within 6 months of treatment initiationSafety indicators: Hepatic and renal function, routine blood results and routine urine results will be assessed at baseline and at the treatment endpoint.

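### The only numeric renal exclusion limit is printed in mmol/L, a creatinine level no patient can reach, so the number as written excludes nobody

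*Protocol article*

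**What the plan says.** In the Recruitment section, the last exclusion criterion covers comorbidities. It opens with a named exclusion, "Those with other comorbidities, such as chronic kidney disease and liver disease", and then gives laboratory limits. The hepatic limit is a multiple of the upper normal limit, so it does not depend on a unit. The renal limit is absolute: "Renal inadequacy: serum creatinine level ≥133 mmol/L". It is the only creatinine limit, and the only numeric renal limit, in the article.

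Renal function appears again under Secondary endpoints as a safety indicator, with neither limit nor unit: "Hepatic and renal function, routine blood results and routine urine results will be assessed at baseline and at the treatment endpoint". The Intervention section adds that "All participants will receive losartan as the background antihypertensive therapy throughout the study period". According to Trial status, version 1.2 of the protocol was approved and 40 patients had been recruited.

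**The concern.** Millimoles per litre is the wrong order of magnitude for serum creatinine. A threshold that no one can reach is not a threshold, so the numeric part of the renal exclusion has no effect if it is applied as printed.

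Three things make this more than a cosmetic matter. The criterion is a safety-related eligibility rule in a trial that gives losartan to every participant, and renal function is one of the trial's own safety indicators. Failing the eligibility criteria after inclusion is also a reason for withdrawal, and under the printed limit no creatinine value could trigger it. Finally, recruitment is under way: with 72 planned and 40 recruited, 72 − 40 = 32 patients were still to be screened when the article was written.

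**Working it through.** **Inputs**
- Printed limit: 133 mmol/L, from the exclusion criteria in the Recruitment section.
- Molar mass of creatinine: 113.12 g/mol. This is an assumption, because the article does not give it; 113 to 114 g/mol is used as the range.

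**Formula:** mass concentration (g/L) = molar concentration (mol/L) × molar mass (g/mol); g/L × 100 = mg/dL.

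**As printed, in mmol/L**
- 133 mmol/L = 133,000 μmol/L.
- 0.133 mol/L × 113.12 g/mol = 15.04 g/L, about 1,504 mg/dL.
- Range for a molar mass of 113 to 114 g/mol: 15.03 to 15.16 g/L.
- About 15 g of creatinine in each litre of serum is not compatible with life. The share of candidates excluded by the number is 0%.

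**Same number read in μmol/L**
- 133 μmol/L = 0.133 mmol/L.
- 0.000133 mol/L × 113.12 g/mol = 0.01504 g/L, about 1.50 mg/dL.
- Ratio of the two readings: 133,000 / 133 = 1000.

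This shows only that the printed number can exclude someone in μmol/L and cannot in mmol/L. It does not establish what limit was intended.

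**Could the micro sign have been lost when the text was read from PDF?** The sign survives under Secondary endpoints, in "HOMA-IR = FBG (mmol/L) × FINS (μU/mL)/22.5", where mmol/L is also printed correctly for glucose. A general loss of the character is therefore unlikely, although a single-character fault in this one place cannot be fully excluded. No other section gives a different unit for creatinine.

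**Effect on the statistics.** The creatinine limit does not enter the assumed response rates, alpha, power, allocation ratio or dropout allowance. No sample-size or analysis figure changes.

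**The case against.** The strongest reply is that the renal exclusion does not fail. The criterion excludes chronic kidney disease by name, whatever the creatinine unit. Eligibility is assessed by the principal investigator and a trained attending physician, and renal function is measured in the hospital's own clinical laboratory. Anyone comparing a laboratory result with 133 would very probably notice the wrong prefix. The article has other language slips, which makes an error confined to the publication plausible.

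Most of this stands, and it limits the consequence. It does not remove the error. The named exclusion carries no stage, filtration rate or other number, so without a usable creatinine limit it rests on clinical judgement. A safety criterion should not depend on readers silently correcting it.

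A reader might infer three stronger things that the article does not support:
- **That renal patients go unscreened.** The named exclusion of chronic kidney disease contradicts this.
- **That a data-system check is disabled.** The data management section mentions only general rules, valid values and scope checks. It does not mention creatinine or say that the checks enforce eligibility, and the case report form is not shown.
- **That some of the 40 recruited patients were wrongly enrolled.** Nothing indicates that anyone was screened against the misprinted unit.

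**Conclusion.** The article states an eligibility limit wrongly. The printed renal limit is 1000 times the same number in μmol/L and, taken literally, excludes no one. The conclusion rests on the unit as printed and on the molar mass of creatinine, and no plausible value of the molar mass changes it.

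A unit-prefix slip is the probable explanation, and the practical impact is likely to be low to moderate. The misprint is well established; a failure of safety screening is not. Whether the slip reaches trial conduct depends on the approved protocol, the case report form and the data system, none of which is shown. The point has no bearing on sample size, power or inference.

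**What to change.** 1. Compare the creatinine unit in the article with the approved protocol (version 1.2), the case report form and any range check for creatinine in the data system. Correct it wherever it is wrong. The intended limit and unit must come from the approved protocol and not be inferred from this article.
2. Only if the operative documents carry the same error, list the baseline creatinine of all patients already recruited (40 at the time of writing) against the confirmed limit, and report any deviations.

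The cost is a one-word correction in the article. If step 2 applies, add corrections to the operative documents, an update to the range check if one exists, and one data listing. The design and analysis do not change.
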